# Methodology

This proposal seeks to evaluate four models of streamlined HIV care that reduce the substantial time and cost currently incurred by patients seeking care. These four models are (1) community adherence groups (CAG), (2) urban adherence groups (UAG), (3) Fast-Track clinic visits and (4) streamlined ART initiation (START). We assess the first two models (CAG and UAG) using a cluster-randomized design because existing observational data already exist. The second two models (Fast-Track and START), for which there is little to no observational or implementation data, will be evaluated using an observational approach, in which selected clinics will implement the model and changes in the outcome will be compared to changes in other clinics not implementing the model through a difference in difference approach. Overall these four models enable greater effectiveness and efficiency of care delivery through tailoring delivery approach to patient needs.

## 3.1 Objective 1: To determine the acceptability, appropriateness, and feasibility of elements of a differentiated care system in Zambia.

### 3.1.1 Methodology for Objective 1

A mixed methods approach will be used to qualitatively and quantitatively evaluate perceptions regarding current challenges in accessing and adhering to life-long HIV treatment and to assess needs and preferences for various potential differentiated care models. We will assess perspectives from three key groups: (1) individual patients and family members (demand side) (2) health facilities –professional and community health workers (supply side) (3) government and local leaders. Four types of cross-sectional data collection methods will be utilized: in-depth interviews, focus group discussions, surveys, and discrete choice surveys. These will form the basis for sequential analysis of supply and demand side factors that may influence the uptake of specific differentiated care models.

### 3.1.2 Population

Critical government (MoH, MCDMCH) and non-government stakeholders involved in the delivery of HIV or other relevant community based services will be targeted for participation. From MoH we will seek participation from Directors (or their delegated representatives) from the Directorate of Clinical Care and Diagnostic Services and Directorate of Policy and Planning in addition to the National ART Program Coordinator. From MCDMCH we will seek interviews with the Permanent Secretary (or delegated representative), Monitoring and Evaluation officer, and the District Medical Officers in all areas where the study takes place. We will also interview both professional and lay health workers presently working under the ART program at the facilities. Pre-ART and patients on ART will also be included. To determine family preferences, we will include a sample of persons living in the same household as a current ART or pre-ART patient registered at a health facility selected for participation.

### 3.1.3 Measurements and Procedures

For Objective 1 we will utilize a combination of: In-Depth Interviews (IDIs), focus group discussions (FGDs), medical chart reviews, discrete choice experiments and a general survey.

*IDI:* Interviewers will utilize semi-structured question guides that are developed based on a review of regional literature and investigator experience and will be specific to the type of participant. Participants will be interviewed for approximately 1 hour and interviews will be conducted in English or a local language (Nyanja, Bemba, or Tonga). Where permission is granted, interviews will be audio-recorded for later transcription and analysis. Participants will be given travel reimbursement (ZMK50, equivalent to ~$7) if participation in the interview required them to travel.

*FGDs:* These will utilize semi-structured question guides that are developed based on a review of regional literature and investigator experience and will be specific to the type of participant. FGDs will last for 1-2 hours and will be conducted in English or a local language (Nyanja, Bemba, or Tonga) based on participant preference. All discussions will be facilitated by a trained discussant fluent in the local language and in English and, where permission is granted, discussions will be audio-recorded for later translation, transcription, and analysis. The discussant will provide ground rules for the discussion before beginning and will be responsible for re-directing the conversation if it goes off-topic. Participants will receive a nominal travel reimbursement (ZMK50 equivalent to ~$7).

*General survey:* We will utilize a cross-sectional survey to measure patient access and psychosocial needs. Access needs will be assessed with questions that address the following: appropriateness of current clinic operating hours; distance, cost, and time required to get to clinic; household income, assets, and expenditures; and opportunity costs of a clinic visit. We will carefully elicit patient costs on a comprehensive set of items related to health care utilization, including transport, communication, and food costs. To assess psychosocial needs we will apply previously validated scales and indices to measure stigma (Revised Berger), depression (PHQ-9), alcohol consumption (AUDIT-C), and domestic violence. The survey will take approximately 30-45 minutes to complete and will be administered by trained survey enumerators using tablets. The survey enumerator will read each survey question and all possible answers choices. Surveys will be conducted in the local language or English, based on the participant’s choice. Survey will initially be written in English, translated into the local language (including Nyanja, Bemba and Tonga) and then back- translated into English to ensure accuracy. Survey responses will be entered directly into the tablet by the survey enumerator and at survey completion all responses will be uploaded to the central database.

*Medical record review:* We will utilize the existing electronic clinical information system (SmartCare) to evaluate patient clinical needs. We will assess distribution of clinical needs over several dimensions: 1) degree of immunosuppression at entry into care (CD4, WHO Stage), 2) frequency of opportunistic infections (OIs) after treatment initiation, and 3) frequency of “ill” versus “healthy” visits.

*Discrete choice survey:* We will use Discrete Choice Surveys (DCSs) to assess patient preference for different, discrete characteristics of various models of community-based ART delivery. We will select key attributes (or aspects) of community-based ART models (i.e. frequency of facility visit, method of ART pick-up, type of health care worker, etc). Additionally, we will select the number of levels (or options) for each attribute (i.e. for frequency of facility visit: every 3 months or every 6 months). These will be used to create a list of all possible combinations. We will divide the subset of combinations chosen in blocks, so that each participant is only asked one possible block of the subset for a total of approximately 10 questions each.

### 3.1.4 Analytic Approach

Qualitative data will be imported into software for managing qualitative analysis (e.g. N-Vivo or Atlas TI) and then subjected to an iterative process of coding using a multi-step process of deductive and inductive techniques. Qualitative data will be cross-referenced to inform and build on the data relating to preferences identified by the quantitative survey and DCSs. Where possible, descriptive statistics and linear regression modeling of scale scores will be utilized to analyze the data. For the discrete choice survey we will estimate main effects plus two-way interactions between different parameters. We will use a nested logit framework for estimation.

### 3.1.5 Sampling Approach/Sample Size Considerations

We have used convenience sampling to determine the number of interviews and focus groups to be conducted (see 1-6 below)

1. Government and community leaders: 20 interviews or until thematic saturation is reached.

2. Professional HCW: two focus group discussions will be conducted (one in an urban clinic and one in a rural clinic) in each province (EP, SP and LP).

3. Lay/Community HCW: two focus group discussions will be conducted (one in an urban clinic and one in a rural clinic) in each province (EP, SP and LP).

4. Patient family members: two focus group discussions will be conducted (one in an urban clinic and one in a rural clinic) in each province (EP, SP and LP).

5. ART patients: four focus group discussions will be conducted (two in an urban clinic and two in a rural clinic) in each province (EP, SP and LP).

6. Pre-Art patients: two focus group discussions will be conducted (one in an urban clinic and one in a rural clinic) in Lusaka province only.

We used the following sample size considerations to determine the number of surveys to be conducted:

General survey: 1,600 patients (of which 800 are ART and 800 are pre-ART).

To derive this sample size we considered a precision approach and calculated the number of ART participants necessary to estimate a binary indicator with 5% margin of error and 95% confidence interval. It is a common practice to assume a prevalence p=0.5 when several indicators are of interest, because p=0.5 is the most conservative choice. We also assume a design effect of 2 since our sampling is clustered at the facility level, and there is significant variability across facilities. Using the formula, we get: n=((1.96^2) * 0.5* 0.5 *2)/(0.05^2)=768, which we approximate at 800. The calculation is repeated for pre-ART patients.

## 3.2 Objective 2: To evaluate the effectiveness, efficiency, and health care quality of a differentiated system of care that includes targeted models of care.

Overall, this objective seeks to evaluate the effectiveness of a differentiated system of HIV care delivery in which the frequency, type, or intensity of contact with the health system is tailored to patient needs. The differentiated system of care includes targeted evaluation of three care models targeting patients stable on ART [community adherence groups (CAGs)], urban adherence groups (UAGs), and fast-track clinic visits), complemented by a model designed for HIV infected patients not yet on therapy (streamlined ART initiation (START)). An overview of these models is available in Appendix 4. These models will be implemented simultaneously, and will be evaluated using a common evaluation framework that includes effectiveness (with a primary outcome of retention), efficiency, and quality.

Patients who meet eligibility criteria, express willingness to participate, and provide written informed consent at the selected intervention sites will be enrolled. Interventions will be targeted by the type of site (rural/urban, high/low volume), baseline retention at site, and by patient status (treatment naïve vs experienced, stability on treatment).

### 3.2.1 Methodology for Objective 2

To evaluate the effectiveness, efficiency and quality of the differentiated care models, a matched cluster randomized design approach is proposed for the CAG and the UAG models, due to substantial weaknesses in existing regional observational pilot data in various settings. Cluster level analysis is being pursued as introduction of the intervention occurs at the clinic level. Randomization is being proposed to account for selection bias encountered in previous observational analyses. As there is little to no observational or implementation data for the Fast-Track and START models, and the goal is to generate such data in Zambia, a difference-in-difference design will be used to calculate the effect of the models on the outcomes of interest.

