### 3.2.5 Analytic Approach and Sample Size Considerations

*a. Outcomes and Analysis*

The primary outcome in three models that target retention in care (CAG, UAG, Fast-track) is defined as time to first missed pharmacy pick-up (> 7 days late). For the START model which targets ART initiation, we use the date of ART initiation as the primary outcome. To evaluate the impact of CAG and UAG interventions, we will use Kaplan-Meier estimates of time to the primary outcome, stratified by intervention condition, using log rank tests. For Fast-track and START, our primary analysis will take a difference-in-difference approach in which we estimate the difference in the change in the rate of the outcome between intervention and control settings. In secondary analyses of the primary outcome, we will explore longer intervals of lateness that comprise a missed pharmacy visit (14 and 30 days) as well as adjustment for baseline patient characteristics. We will also explore analysis using medication possession ratio (MPR) as the outcome and other metrics of retention ^17^ that incorporate both frequency of missed visit as well as interval of time before return.

The secondary outcomes will focus on implementation and quality (see Appendix 2).

a. *Implementation Outcomes*

- *Feasibility* will be evaluated qualitatively through analysis of interviews and focus groups.
- *Costs* will be evaluated quantitatively using “bottom-up” activity-based micro-costing techniques (see Measurements section above) and “top-down” evaluation of budgets and spending reports, based on calculations of DALY’s.
- *Fidelity* of the intervention models will be assessed through estimates of the proportion of identified and eligible patients successfully enrolled in a model, the proportion of missed visits, and the proportion of CAG/UAG still functioning at the end of the 12-month intervention period.

*b. Quality Outcomes*

We use the framework offered by the Institute of Medicine to define quality outcomes.:

- *Access* will be evaluated using time (days) from positive symptom screen to appropriate referral.
- *Efficiency* will be assessed using cost-effectiveness analysis. We will consider the incremental cost per additional patient retained and the cost per death averted using effectiveness data from each model.
- *Safety* will be evaluated by estimates of the proportion of patients with appropriate laboratory monitoring and symptom screening.

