- *Equity* will be assessed by comparing retention rates between adults and adolescents and men and women.
- *Patient-centeredness* will be assessed through comparison of means in the results of appropriate dimensions in the semi-structured patient exit-survey.

*c. Patient Outcomes*

- HIV RNA: we compare the proportion of patients suppressed at one year among those exposed to the intervention and control conditions using mixed effects logistic regression
- Satisfaction: we will compare the effect of the intervention on patient satisfaction through mixed effects linear regression.

1. *Sample Size Considerations*

- CAG/UAG: Existing program data suggest that 65% of patients are at least 7 days late for a pharmacy refill visit during their first year in HIV care after starting ART and that 95% of clinics fall within 15% (that is 50 to 80) of this estimate. Thus, a conservative matched co-efficient of variation is estimated to be 0.10. We assume a 50% reduction in missed pharmacy visits due to CAG and UAG. Under these assumptions, for the CAG intervention, our selection of five clinics and 120 patients per site (in 20 CAGs per site assuming complete enrollment), the study will be powered at 96%. Under more conservative assumptions about between clinic variability and the effect size (Appendix 6) this sample size yields power of over 80%. For the UAG intervention, our target sample size is 4 UAGs at each of the five intervention sites with 30 people in each UAG and therefore 120 participants per site (total of 600 participants across sites). Under the same assumptions about coefficient of variation and the effect size as for the CAG model, this sample size yields power of > 90% and is robust to varying assumptions about correlation (See Appendix 6).
- Fast-track: Our target sample size for Fast-track is 200 patients at each of four sites (two intervention sites and two control sites; n=800 total). Assuming baseline 80% of patients miss a pharmacy visit in a year of care, which we anticipate will fall to 40%, we have 80% power.
- START: Assuming ART initiation at 2 weeks rises from 60% to 85%, 100 patients at each of eight sites (four intervention and four control sites; n=800 total), rho of 0.15 yields an anticipated power of 78%. No more than 200 patients will be enrolled into the study to receive POC CD4 testing with their consent. Enrolment will stop when we reach 100 patients who are eligible for ART initiation.

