## 7. 4 Appendix 4: Overview of four models of differentiated care implemented in Objective 2

| **Model** | **Location** | **Number of sites** | **Number groups per site** | **Total sample size** | **Problem(s) addressing** | **Description of model** | **Selected related literature** |
| --- | --- | --- | --- | --- | --- | --- | --- |
| Model 1: Community adherence groups (CAGs) | Rural | 5 | 20 groups of 6 patients | 600 | Poor adherence and retention; long patient travel time and cost; rural clinic congestion and wait time | Monthly patient ART groups, facilitated by lay counselor, meet at location of group’s choice. Patients travel to clinic once every six months (rotating between group members) for labs and to pick up medications. | Decroo et al, 2011  Rasschaert et al, 2014 |
| Model 2: Urban adherence groups (UAGs) | Urban | 5 | 4 groups of 30 patients | 600 | Poor adherence and retention; long patient wait time and cost; urban clinic congestion | 2-3 monthly patient ART groups, meet during off-hours at clinics. Adherence discussion by lay ART counselor; ARVs distributed by pharmacy technician. Patients schedule clinic visit once every six months. | Luque –Fernandez, 2013 |
| Model 3: FAST-TRACK | Urban | 2 | N/A | 400 | Urban clinic space limitations/ congestion; wait time; poor retention | Container unit or dedicated room at clinics provide ART patients with rapid refills and health checks, facilitated by use of electronic health card. | McGuire et al, 2011  CIDRZ/MIT operational observation |
| Model 4: START | Urban & rural | 4 | N/A | 400 | Poor retention in newly eligible patients; clinic congestion and wait time | Patients testing positive will be given an option to move into a streamlined process wherein substantial counseling is delivered, as well as necessary baseline safety laboratory tests and ART is provided as soon as possible after being classified as eligible to initiate ART per guidelines. | Karim, 2009  Blanc, 2010  Amuron, 2009  Geng, 2011 |

## 7.5 Appendix 5: Routine schedule of activities within four models of differentiated care implemented in Objective 2

| Model | Frequency of Activity (interaction) | Symptom Screen | Interaction with clinician | Drug dispensation | Primary HCW Interaction |
| --- | --- | --- | --- | --- | --- |
| 1: Community Adherence Group | Monthly | Every visit | Every 6 months or acute event | Monthly | Lay health care worker |

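### Fast-Track sites may be chosen partly on baseline retention and are then judged, without randomisation, on change in pick-up retention, which leaves the estimate open to regression to the mean

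*Protocol*

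**What the plan says.** Section 3.2 sets the targeting rule for all models together: "Interventions will be targeted by the type of site (rural/urban, high/low volume), baseline retention at site, and by patient status". It gives no direction, cut-off or definition for the retention criterion.

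Section 3.2.1 reserves randomisation for two models: "a matched cluster randomized design approach is proposed for the CAG and the UAG models". For Fast-Track and START, section 3.0 says that "selected clinics will implement the model and changes in the outcome will be compared to changes in other clinics not implementing the model". No rule for choosing those other clinics is given.

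Section 3.2.5 makes difference-in-difference the primary Fast-Track analysis: "we estimate the difference in the change in the rate of the outcome between intervention and control settings". The outcome is a pharmacy pick-up more than 7 days late. The planned size is "200 patients at each of four sites (two intervention sites and two control sites; n=800 total"), and the control data are routine aggregates.

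Appendix 4 lists the problems that Fast-Track addresses as "Urban clinic space limitations/ congestion; wait time; poor retention".

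**The concern.** Difference-in-difference removes stable differences in level between clinics. It does not remove a temporary one. A clinic chosen because its baseline year was unusually poor can be expected to look better the next year with no intervention, and a clinic not chosen that way has no such expectation. The gap between the two drifts enters the estimate as if it were an effect.

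CAG and UAG are protected, because there randomisation decides which of the targeted clinics receive the model. START is less exposed, because its outcome is ART initiation rather than retention. Fast-Track has the exposed combination: a retention-related selection criterion, a retention-related outcome and no randomisation.

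With two clinics per arm there is little to average over. Enrolling more patients per clinic does not remove real year-to-year drift, and the standard error does not reveal the bias. The estimate also feeds the planned cost per additional patient retained.

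**Working it through.** **The plan's own figure.** For Fast-Track the protocol says: "Assuming baseline 80% of patients miss a pharmacy visit in a year of care", "which we anticipate will fall to 40%, we have 80% power". This power cannot be reproduced, because no between-clinic correlation is given for Fast-Track. With 400 per arm and a design effect of 1 + 199ρ (two-sided 0.05), power is about 100% at ρ = 0, 55% at ρ = 0.15 (the START value), and 80% only at ρ of about 0.085. The present point does not depend on it. What matters here is the planned effect: 80 − 40 = 40 points.

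**Inputs from section 3.2.5.** The programme mean is 65% late, and 95% of clinics lie between 50 and 80%. The between-clinic SD is therefore about 15/2 = 7.5 points. These figures describe the first year after starting ART, whereas Fast-Track requires at least 6 months on ART, so they are indicative only.

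**Assumed, not in the protocol.** Year-to-year clinic correlation r of 0.5 to 0.8; 6 to 20 candidate clinics; the two worst chosen on the outcome measure itself; the selection year is also the analysis baseline; no true effect.

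**Formula.** With equal spread in both years, a clinic's expected change is −(1 − r) × (baseline − mean). The expected difference-in-difference is therefore −(1 − r) × (mean baseline of intervention clinics − mean baseline of control clinics).

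**Numbers.** Simulated baseline means (% late) and the resulting spurious difference, in points favouring Fast-Track:

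| Candidate clinics | Two worst | Random controls | Bias, r = 0.5 / 0.8 | Next-worst controls | Bias, r = 0.5 / 0.8 |
|---|---|---|---|---|---|
| 6 | 72.2 | 61.4 | 5.4 / 2.2 | 65.0 | 3.6 / 1.4 |
| 10 | 74.5 | 62.6 | 5.9 / 2.4 | 68.9 | 2.8 / 1.1 |
| 20 | 77.3 | 63.6 | 6.8 / 2.7 | 72.7 | 2.3 / 0.9 |

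Check by hand for 10 clinics and r = 0.5: 0.5 × (74.5 − 62.6) = 5.95 with random controls, and 0.5 × (74.5 − 68.9) = 2.8 with next-worst controls.

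**Sensitivity.**
- At r = 0.9 the bias with random controls is 1.1 to 1.4 points.
- If the selection score correlates only 0.5 with baseline lateness, because several criteria are used, the bias with random controls is 1.1 to 3.4 points over r = 0.8 to 0.5.
- If intervention and control clinics come from the same worst-retention set and are split at random, it is 0.0.

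**Scale.** The SD of one clinic's change is 7.5 × √(2(1 − r)), and the difference between two two-clinic means has the same SD: 4.7 points at r = 0.8 and 7.5 at r = 0.5. The bias stays below one such SD throughout. Against the planned fall, 2.2/40 to 6.8/40 is about 5% to 17% with random controls, and 0.9/40 to 3.6/40 is about 2% to 9% with next-worst controls.

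**The case against.** A reader might infer that regression to the mean will be counted as a Fast-Track effect. The protocol does not support that. It would require four things, none of them stated: low-retention clinics receive the model; the controls sit at a different baseline level; the selection period is also the analysis baseline; and targeting uses the same measure as the outcome. On the last, the background sections use retention to mean remaining in care, whereas the outcome is a late pick-up. If the two measures differ, only the transient error they share would regress.

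The targeting sentence is also general. It lists site type, volume and patient status beside retention, and may mean fitting models to kinds of site rather than picking the worst clinics. In Appendix 4, poor retention comes last for Fast-Track, after space, congestion and waiting time. The 80% planning baseline lies at the upper edge of the 50 to 80% range, which is compatible with poor performers being chosen, but that range describes a different treatment period.

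The observational design was chosen openly, to generate first data, and an analysis plan could fix the pre-period.

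All of this stands, and it makes the point conditional. It does not remove it. Baseline retention is a stated criterion, and the choice of sites and controls is a design decision that an analysis plan written later cannot undo.

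**Conclusion.** The protocol leaves the Fast-Track estimate open to regression to the mean and names no safeguard. Whether the bias arises, and in which direction, depends on choices that the protocol neither states nor rules out. Appendix 4 suggests that poor performers might be chosen, which would favour Fast-Track; choosing good performers would reverse the sign.

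Under the worst-two assumptions the size is about 2 to 7 points with random controls and about 1 to 3.6 with next-worst controls. It is smaller if selection rests on several criteria or on a different retention measure. A bias of this size could not produce a 40-point fall, but it would distort a modest true effect and the cost per additional patient retained. The correlation and the number of candidate clinics are assumptions, and the 7.5-point SD is borrowed from first-year ART patients.

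**What to change.** Make two changes to the Fast-Track design text in sections 3.2 and 3.2.5:

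1. Choose the control clinics by the same site criteria as the intervention clinics, including the same baseline-retention range, and state that range and the measure used.
2. Take the difference-in-difference baseline from a routine-data period not used to select sites, or use several pre-periods.

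With equal baselines the expected bias in the formula above is zero, provided both arms come from the same pool of urban clinics. The separate baseline guards against the case where they do not.

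The cost is protocol wording, some loss of freedom in choosing control sites, and one further period of routine data, whose availability at the candidate clinics must be confirmed. No extra patients or visits are needed, since Fast-Track controls are not enrolled. Allocating the model by lot among qualifying clinics would also remove the problem, but it replaces a deliberate observational design and is optional.
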